#### Data analysis.

After data collection is complete, information will be cleaned and stored on the private and secure computers of the research team. Responses will be reviewed to further refine the item pool. The study team will review descriptive and qualitative feedback to identify problematic items that need revision. The content validity index (CVI) will determine the relevance of items, evidence of the validity of the content [67] and retention of items in the tool [68]. At the end of the second expert panel review, items with an CVI < 0.78 will be considered problematic and will be deleted or modified.

### Phase 3: A focus group discussion with the PC experts

Clinical voices of PC experts and nuances of the readiness concept may not be fully explored in an online survey. Therefore, a one-time focus group [69] will be conducted with an expert panel to obtain additional insights on the important aspects of the PC content and its relevance to older adults with cancer. We will also incorporate clinician/health system barriers into the discussion during this focus group session. Further, we will gather perspectives from these experienced physicians, nurses, social workers, and chaplains who have observed how patients evolve in their understanding of PC. Finally, we will gather information on what interventions regarding readiness for PC would be useful in clinical settings to gather ideas for future intervention development after all the psychometric properties of this readiness tool have been established.

#### Recruitment.

The same group of experts who participated in the online survey will be invited to participate in the focus group discussion with a sample goal of 6 participant informants.

#### Data collection.

After obtaining the informed consent, the focus group discussion will be moderated by the PI using a semi-structured interview guide and is anticipated to last for approximately 60 minutes. The research team will develop clarifying and open questions regarding each item on the initial PALCARE tool from the online expert panel review survey. The focus group will be conducted virtually and audio recorded. The audio files will be transcribed and fully de-identified before analysis.

#### Data analysis.

After the focus group, the moderator will debrief with other members of the research team to identify and note initial impressions and critical points of the conversation. Data will be analyzed using focus group methodology that includes a) familiarization, b) indexing, c) charting, d) mapping, and e) interpretation [69].

### Phase 4: Cognitive interviews with older adults with cancer and their family caregivers

Cognitive interviews will be conducted with 20 dyads of older adults with cancer and their family caregivers. The NCP guidelines [54] have emphasized that family caregivers are an integral part of palliative and hospice care services alongside patients with serious illnesses. Especially for older adults with cancer, family caregivers can provide information about their health and function. They also can help older adults better understand PC. It, therefore, is essential that family caregivers be involved in understanding readiness for PC in older adults with cancer [70]. Caregivers will include self-endorsing or identified by the patient as an unpaid spouse/partner, relative, or friend who has a close relationship with them, assists them in their medical care, and does not have to live in the same household [71]. To get individual perspectives from the caregivers, we will conduct cognitive interviews separately with the older adults with cancer and their caregivers. Including family caregivers’ perspectives will help us understand the congruence/incongruence about readiness for PC and inform not only the development of the readiness tool but also the administration of the tool (timing, mode of delivery) and future interventions.

Cognitive interviews help researchers develop items for an instrument that are appropriate, comprehensive, and easily understandable by the participants in the target population [72]. Cognitive interviewing uses a combination of verbal probing and think-aloud alone techniques [73]. This process helps researchers understand participant’s decisions by examining the thought processes behind their responses. Verbal probing allows for clarification and comments on wording of question items [74]. Think-aloud technique helps researchers understand what kind of information the participants remember while answering a question [73]. Cognitive interviews improve the validity and reliability of a survey in two ways: (a) provide additional evidence on items that address salient aspects of participants’ experiences and further strengthen the content validity; (b) help refine ambiguously or poorly worded items and enhance questionnaire reliability [73].

#### Recruitment.

Cognitive interviews will be conducted in 20 older adults with cancer and 20 family caregivers. Participants will be purposively selected to reflect a diversity of cancer types, race/ethnicity (White, Black, Hispanic), and rural versus urban residence. Criteria for family caregivers include a) Being at least 18 years of age; b) Identifying themselves as the family caregiver or being identified as such by the older adult with cancer; c) Ability to communicate in English. Each participant will receive a $50 Amazon gift card as a thank you for completing the survey.

#### Data collection.

After obtaining informed consent, PALCARE items will be evaluated using cognitive interviewing techniques with a sample of 20 dyads of older adults with cancer and their family caregivers. The substantial sample size of n = 40 for the cognitive interviews will enable us to identify potential problems with the questions and maximally fine-tune the tool [75]. Verbal probing approach of cognitive interviews will be used to solicit the participants’ understanding and interpretation of each item in the PALCARE tool. Verbal probing will allow participants to ask for clarification and comments on wording of each item in the PALCARE tool. We will randomly order the items in the PALCARE tool to ensure the eight PC domains are dispersed throughout the questionnaire [72]. During the cognitive interviewing process, the interviewer will read each question to the participants and ask that they verbalize their understanding of each question. The cognitive interviews will be conducted using a structured interview guide according to the established standard guidelines for cognitive interviewing [74]. According to the guidelines, the cognitive interview will consist of the following process: (a) a PALCARE item will be asked, and the respondent will respond; (b) a series of verbal probes will be asked in reference to that PALCARE item and the respondent’s answer; (c) this process will be repeated for each PALCARE item. Probes will be developed to evaluate several features relevant to item structure and respondent decisional processes according to the verbal probing guidelines provided by Willis, 2005 [74] and will be applied consistently across all PALCARE items. All interviews will be audio recorded.

To help establish preliminary a) convergent validity of the PALCARE tool with the global question on PC readiness from the Perceptions of Palliative Care Instrument (PPCI) [53], and b) test-retest reliability by repeatedly assessing PALCARE before the cognitive interview and 2 weeks afterward, we will ask participants to a) rate their PC readiness using the one question from the PPCI instrument “How ready are you to hear about palliative care today?” (Scoring option, 0 = not at all to 10 = totally); and b) rate their PC readiness using our PALCARE tool before the cognitive interview and 2 weeks after the cognitive interview.

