#### Aim 3.

Establish preliminary convergent validity and test-retest reliability of the PALCARE tool: We will assess a) convergent validity of the PALCARE tool by correlating the PALCARE with the global readiness to hear about PC from the Perceptions of Palliative Care Instrument (PPCI) [53], and b) test-retest reliability by assessing readiness for PC using the PALCARE tool during the cognitive interview and 2 weeks afterward.

The three specific aims which will be conducted over 4 phases (see Table 1).

**Table 1 pone.0323366.t001:** Overview of methods/specific aim for each study phase.

Specific Aims	Study phase
1) Develop PALCARE tool	**Phase 1**: Semi-structured interviews with a diverse group of 20 older adults with cancer (White, Black, and Hispanics)
2) Establish the content validity of the PALCARE tool	**Phase 2**: Two rounds of expert panel survey with 10 PC experts; **Phase 3**: Focus group with 6 PC experts **Phase 4**: Cognitive interviews with 20 diverse group of dyads of older adults with cancer and their family caregivers
3) Establish the preliminary convergent validity and test-retest reliability of the PALCARE tool	**Phase 4**: Cognitive interviews with measurement of the global question on PC readiness from the Perceptions of Palliative Care Instrument (PPCI) and repeatedly assessing PALCARE before the cognitive interview and 2 weeks afterward.

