### Eligibility criteria.

Participant eligibility will include the following: a) ≥60 years, b) diagnosis of advanced cancer (metastatic, stage III or IV solid tumors), c) no current enrollment in hospice care; d) ability to communicate in English. Exclusion criteria include a) those under age 60 years, b) non-advanced cancer, c) enrolled in hospice care, d) inability to communicate in English, and e) cognitive impairment as indicated by the Callahan assessment tool [62]. We selected the age criteria of 60 years and above for recruitment because recent evidence suggests that geriatric impairments and frailty are prevalent and commonly occur in individuals as early as age 60 years [63]. Also, cancer occurs in much earlier age among patients belonging to racial/ethnic minority backgrounds [64].

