#### Data analysis.

Audio recordings of the cognitive interviews will be transcribed and fully de-identified. Several procedures will be followed to ensure rigor and adherence to the cognitive interview procedure and appropriate verbal probing. Each researcher will review results to make decisions on revising, retaining, deleting, or adding items in the PALCARE tool. As recommended by previous literature, we will review each item to examine participants’ understanding and ability to respond to each item. Correlations of the PALCARE and the global readiness will be used to demonstrate convergent validity. Correlations of the two assessments of PALCARE will be used to demonstrate test-retest reliability. In addition, we will compare the scores across pretest and posttest using paired-samples t-tests.

The Question Appraisal System (QAS) [76] will be used to analyze the interview data and identify sources of response bias within and across the PALCARE items. The QAS is a coding tool used to evaluate questions based on prespecified types of problems within categories. The QAS has eight problem categories: a) reading; b) instructions; c) clarity; d) assumptions; e) knowledge/memory; f) sensitivity bias; g) response categories; and h) other. The first QAS category targets researchers and is not applicable to older adults with cancer. Thus, we will examine each PALCARE item for the seven remaining QAS problem categories. Each category has multiple specific problem types that could be identified [75]. Decisions of retaining, revising, or deleting items will depend on its importance or relevance to PC readiness in older adults with cancer, clarity of instructions to complete the survey, difficulty of items etc. The eight problem categories of QAS and their description are listed in Table 3.

**Table 3 pone.0323366.t003:** QAS Overall Categories and Their Description.

QAS Category	Description
1. Reading	Determine if it is difficult for the interviewers to read the question uniformly to all respondents.
2. Instructions	Look for problems with any introductions, instructions, or explanations from the respondent’s point of view.
3. Clarity	Identify problems to communicating the intent or meaning of the question to the respondent.
4. Assumptions	Determine if there are problems with assumptions made or the underlying logic.
5. Knowledge/memory	Check whether respondents are likely to not know or have trouble remembering information.

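### The two-week retest, as described, has no measure of who stayed stable, so true change that differs between respondents cannot be told apart from measurement error in PALCARE.

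*Protocol article*

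**What the plan says.** Under Phase 4, Data collection, the article sets out to establish "test-retest reliability by repeatedly assessing PALCARE before the cognitive interview and 2 weeks afterward", for which participants are to "rate their PC readiness using our PALCARE tool before the cognitive interview and 2 weeks after the cognitive interview". Table 1 likewise describes PALCARE as the repeated measure. It gives the single global item from the Perceptions of Palliative Care Instrument (PPCI) as a measurement without a repeat, and the text assigns that item to convergent validity. The Phase 4 sentence could be read as covering both measures at both times, but it does not say so.

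Phase 4, Data analysis fixes the statistic: "Correlations of the two assessments of PALCARE will be used to demonstrate test-retest reliability". It adds that "we will compare the scores across pretest and posttest using paired-samples t-tests". The type of correlation is not named.

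The sample is given under Phase 4, Recruitment: "Cognitive interviews will be conducted in 20 older adults with cancer and 20 family caregivers". The only disease criterion for patients, "diagnosis of advanced cancer (metastatic, stage III or IV solid tumors", stands under Phase 1, Eligibility criteria. Phase 4 lists criteria for caregivers only.

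The section on the Readiness to Change Framework describes readiness as three successive phases, from realising a need, through weighing costs and benefits, to planning.

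One related point needs reconciling. The Aim 3 text places the first rating differently, "assessing readiness for PC using the PALCARE tool during the cognitive interview and 2 weeks afterward", whereas Table 1 and Phase 4 place it before the interview.

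**The concern.** A test-retest coefficient estimates reliability only among people whose true state is the same on both occasions. Here the construct is described as changeable. The patients are presumably seriously ill, and the cognitive interview, which probes every item, falls between the two ratings. Some respondents may really move in two weeks, for clinical reasons or because of the interview.

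If they move by different amounts or in different directions, the correlation falls even when the tool measures without fault. With only two PALCARE scores per person, a low coefficient would have two explanations that the data cannot separate. The paired t-test does not resolve this. It sees only the mean, so changes in opposite directions cancel out. A mean shift that it does detect could be clinical change, an interview effect or response drift.

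Loss to follow-up adds a further unknown. If patients who deteriorate miss the retest, the remaining pairs are a selected group, and the article describes no record of why retests are missed.

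At stake is the interpretation of Aim 3's reliability result, and with it any decision to rework items that were performing well.

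**Working it through.** The document states no target reliability, expected correlation or precision for the retest, so there is no figure to reproduce. Its one sum is consistent: 20 dyads × 2 = 40 persons. Everything below rests on assumed inputs.

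**Model.** First score X1 = T + e1 and second score X2 = T + C + e2. Here T is the true score, e is error and C is true change, independent of T. Observed variance at the first rating is set to 1, so SDs are in units of the observed-score SD across respondents. With reliability rel,

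expected Pearson r = rel / √(1 + Var(C)).

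**Uneven change.** Let a fraction p change, with mean zero and SD s, so Var(C) = p·s². With rel = 0.85:

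| p | s | Calculation | Expected r |
|---|---|---|---|
| 10% | 1 | 0.85/√1.10 | 0.81 |
| 25% | 1 | 0.85/√1.25 | 0.76 |
| 40% | 1 | 0.85/√1.40 | 0.72 |
| 25% | 0.7 | 0.85/√1.1225 | 0.80 |
| 30% | 0.5 | 0.85/√1.075 | 0.82 |

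In the last row the loss is about 0.03. The same case gives 0.80 → 0.77 and 0.90 → 0.87 at the other two reliabilities tried. If 30% change by 1 SD in mixed directions, those two fall to 0.70 and 0.79.

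**Common shift.** If everyone moves by the same amount d, Var(C) = 0 and Pearson r stays at 0.85. An agreement intraclass correlation would fall to 0.85/(1 + d²/2), which is 0.76 at d = 0.5 and 0.57 at d = 1.

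**Paired t-test.** Take n = 20 patients, a two-sided 5% level (assumed) and SD of the difference √(2(1 − rel)). For rel = 0.80 / 0.90, power for a mean shift of 0.2 SD is 27% / 48%, and for 0.3 SD it is 52% / 81%. Mixed-direction change with zero mean is invisible to this test at any sample size.

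**Sampling error.** The Fisher-z 95% interval is tanh(atanh r ± 1.96/√(n − 3)).
- r = 0.85, n = 20: 0.65 to 0.94.
- r = 0.80, n = 20: 0.55 to 0.92.
- r = 0.80, n = 14 (if 14 of 20 patients were stable, assumed): 0.47 to 0.93.

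All five expected values in the table lie inside the first interval.

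**The case against.** The strongest objection is that this is a condensed article. A change question, an event checklist and a log of missed retests are details that a full protocol may hold, so their absence here does not prove their absence from the study. That stands as a caution. It does not remove the point, because the article does state what is rated at each time and which statistics will demonstrate reliability, and those statistics use only the two scores.

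A reader might infer that true change will necessarily be counted as unreliability. The documents do not support that. A common shift leaves a Pearson correlation untouched, and nothing in the article says how often, or by how much, readiness changes in two weeks. The Phase 3 remark about experts "who have observed how patients evolve in their understanding of PC" concerns understanding, gives no timescale, and is there to justify the focus group.

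A reader might also infer that the reliability part of Aim 3 cannot be answered at all. That is too strong. The article calls this work preliminary, and Future directions defers psychometric validity and reliability to later quantitative studies. A high coefficient would still be informative.

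Three further limits stand. The advanced-cancer criterion is carried over from Phase 1 and does not describe the 20 caregivers. The attenuation is modest relative to sampling error at n = 20. If those who change most also miss the retest, their absence would partly offset the attenuation. Small size is not a full defence, however. Bias adds to imprecision, and stability data not collected at the retest cannot be reliably recovered later.

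**Conclusion.** The point holds in a limited form. As described, the retest gives no means of separating uneven true change from measurement error, and the paired t-test does not supply one. A low coefficient, or a detected mean shift, would be ambiguous.

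The size is not known from the documents. Across the assumed scenarios with reliability 0.85, the expected correlation runs from 0.82 (30% shifting by half an SD) to 0.72 (40% changing, SD of change one observed-score SD). These figures assume change that is independent of the starting level and averages zero. The application to patients also assumes that the Phase 1 disease criterion carries over to Phase 4. This is a worthwhile improvement to a preliminary aim, and it does not invalidate the study.

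**What to change.** At the two-week contact, after PALCARE has been completed so that the answers are not primed:

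- Ask one transition question: less ready, the same, or more ready than last time.
- Record events since the first rating: palliative care consultation, hospice enrolment, hospital admission, and change in disease or treatment status.
- Record the reason for every missed retest.

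Keep the all-pairs coefficient as the main result. Beside it, report the coefficient among respondents who answered the same and had no recorded event, as a sensitivity estimate. Give confidence intervals for both. If the full protocol already collects this information, it is enough to say so and to name the stable-respondent analysis. Reconcile the timing of the first rating between Aim 3 and Phase 4 in the same revision.

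The cost is a few minutes per participant at an existing contact. The stable subset will have a wider interval, as the n = 14 example shows, and is unlikely to settle the question alone. Selecting on self-reported stability may also bias that estimate mildly upward, which is why it should not replace the all-pairs figure.

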### Readiness to Change Framework

Dalton and Gotlieb [39] developed the Readiness to Change Framework which states three phases that characterize the process of readiness prior to a behavioral change: a) realizing what needs to change, b) weighing the cost and benefit, and c) planning for action. The first phase is becoming aware of and realizing what needs to change. The second phase involves appraising the costs and benefits of the proposed change and determining whether to change or not. When an individual decides that the benefits of the proposed change are greater than the costs, the final phase of the readiness process begins. The final readiness phase involves their desire or willingness to change and planning for action towards that change [39]. Using this framework, the readiness for PC among older adults with cancer may occur in three phases: 1) realizing they have high symptom burden and other unmet needs that may benefit from PC; 2) weighing PC costs and benefits of PC; and 3) planning to receive PC.

Fig 1 illustrates the eight domains of PC recommended by the NCP guidelines that PALCARE items will cover and the three phases of readiness that will be used to construct response categories for the questions.

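### The cognitive interview falls between the two PALCARE ratings, so their correlation cannot be read cleanly as test-retest reliability, and the Aim 3 text gives a different order

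*Protocol article*

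**What the plan says.** The protocol article describes the timing of the two PALCARE ratings in three places.

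- **Phase 4, Data collection:** participants "rate their PC readiness using our PALCARE tool before the cognitive interview and 2 weeks after the cognitive interview".
- **Table 1, Phase 4 row for Aim 3:** "repeatedly assessing PALCARE before the cognitive interview and 2 weeks afterward". This agrees with the Data collection text.
- **Aim 3 text:** "test-retest reliability by assessing readiness for PC using the PALCARE tool during the cognitive interview and 2 weeks afterward". This does not agree with the other two.

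Phase 4, Data collection also describes the interview. Each item is asked and answered, then "a series of verbal probes will be asked in reference to that PALCARE item and the respondent’s answer", and this is repeated for every item. In addition, "Verbal probing will allow participants to ask for clarification and comments on wording of each item in the PALCARE tool".

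Phase 4, Data analysis gives the use of the two scores: "Correlations of the two assessments of PALCARE will be used to demonstrate test-retest reliability". It adds that "we will compare the scores across pretest and posttest using paired-samples t-tests". The type of correlation is not named. The article describes no retest without an intervening interview, no check that respondents were stable, and no caveat about the interview.

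**The concern.** A test-retest coefficient estimates reliability only if nothing between the two administrations acts on the construct or on how the items are answered. Here a structured discussion of every item, and of the respondent's own answer to it, always lies between them.

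The protocol's own theory makes an effect plausible. The Readiness to Change Framework section says "The first phase is becoming aware of and realizing what needs to change", and that weighing costs and benefits comes next. The same section says that these phases will be used to build the response categories. An item-by-item discussion across all eight palliative care (PC) domains could therefore move some respondents from one category to another. It could also fix their first answers in memory.

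What is at stake is the meaning of the Aim 3 coefficient. A low value might reflect a noisy tool or uneven change after the interview. A high value might reflect a stable tool or rehearsed answers. An analysis plan written later could not separate these, because each person has only two scores and the interview is always between them.

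**Working it through.** The article states no reliability target or expected correlation, so there is no figure to reproduce. The check uses a simple two-occasion model. Its parameter values are assumptions, and a Pearson correlation is assumed.

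**Model.** First score T1 = X + e1. Second score T2 = X + D + e2. Var(T1) = 1, true reliability is ρ, and D is the interview effect with mean m, SD s and correlation c with the true score X. Then

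r = (ρ + c·s·√ρ) / √(1 + s² + 2·c·s·√ρ).

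The mean m does not appear, so a shift that is equal for everyone leaves r unchanged.

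**No interview effect (s = 0).** r = ρ, for example 0.80.

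**Uneven change unrelated to baseline (c = 0), ρ = 0.80.**
- s = 0.3: 0.80 / √1.09 = 0.77
- s = 0.5: 0.80 / √1.25 = 0.72

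**Sensitivity to c, ρ = 0.80.**

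| s | c = −0.5 | c = 0 | c = +0.5 |
|---|---|---|---|
| 0.3 | 0.73 | 0.77 | 0.80 |
| 0.5 | 0.64 | 0.72 | 0.79 |

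The loss is larger if the interview moves low scorers up most, and close to nil if it moves high scorers up most.

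**Remembered answers.** If s = 0 but the errors on the two occasions correlate at k, then r = ρ + k(1 − ρ).
- k = 0.2: 0.80 + 0.2 × 0.20 = 0.84
- k = 0.5: 0.80 + 0.5 × 0.20 = 0.90

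**Identifiability.** An observed 0.72 fits a true reliability of 0.72 with no interview effect, and equally 0.80 with s = 0.5 and c = 0. An observed 0.84 fits a true 0.84, and equally 0.80 with k = 0.2. The two scores alone cannot tell these apart.

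**Does the paired t-test help?** It addresses only a mean shift, which is the part that leaves r unchanged, and it cannot attribute that shift to the interview. With n = 20 patients, ρ = 0.80 and a mean shift of 0.3 SD:
- s = 0: SD of the difference = √(2 × 0.20) = 0.632, power about 0.52
- s = 0.5: SD of the difference = √(0.40 + 0.25) = 0.806, power about 0.35

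**Precision for comparison.** For r = 0.80 and n = 20, the Fisher interval is tanh(1.099 ± 1.96/√17), that is 0.55 to 0.92.

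**Aim 3 wording.** If the first rating is taken during the interview, each item is still answered before its own probes, but after the probes on all earlier items. The first score would then itself be partly affected by the interview.

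**The case against.** The strongest reply is that little rests on this coefficient. The article calls the reliability work preliminary, and Future directions leaves psychometric validity and reliability to later quantitative studies. Items are kept, revised or deleted on the interview findings and the Question Appraisal System, not on the correlation. This stands, and it lowers the severity. It does not remove the confounding, which would be the same in a larger sample.

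A second reply is that the interview effect is not shown. The probes concern understanding and wording and are not described as PC education. Completing PALCARE already exposes respondents to all eight domains, so some reactivity would remain in any retest. Also, with 20 patients, losses of 0.03 to 0.08 are small against an interval of 0.55 to 0.92. All of this is fair. It means that the size is unknown, not that the coefficient is clean.

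A third reply is that the present order protects the main Phase 4 data. Respondents meet the probes after fewer exposures to the items, and dropout over two weeks loses only the retest. That is a genuine trade-off.

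A reader might also draw three stronger conclusions that the document does not support:
- **That the reliability part of Aim 3 is unanswerable whatever the data show.** This presumes a material effect that differs between people, or a material memory effect, and the article quantifies neither.
- **That a general shift in readiness would spoil the coefficient.** It would lower an absolute-agreement coefficient, but the article names correlations only, and a Pearson correlation is unaffected.
- **That the pretest and posttest labels concede an intervention.** They are ordinary labels for a first and a second score.

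**Conclusion.** The point holds at moderate severity. As sequenced in Phase 4, Data collection and Table 1, the planned correlation combines measurement error with any person-specific interview or rehearsal effect, so it should not be presented as test-retest reliability without qualification. The Aim 3 text contradicts that sequence and needs correcting in any case.

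The direction of bias is not fixed. For a true reliability of 0.80, the illustrative range is 0.77 to 0.72 for uneven change (SD 0.3 to 0.5, unrelated to baseline) and 0.84 to 0.90 for remembered answers (error correlation 0.2 to 0.5). The reliability, the change SDs and the error correlations are all assumptions. The finding itself rests on the stated order of events, not on these values.

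**What to change.** Keep the two contacts and the two-week interval, and move the interview.

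1. **Contact 1:** PALCARE and the global readiness item from the Perceptions of Palliative Care Instrument, with no probing.
2. **Contact 2, two weeks later:** PALCARE again, then the cognitive interview.
3. **Wording:** bring the Aim 3 text, Table 1 and Phase 4, Data collection into line with this order.
4. **Optional:** any question on perceived change, or on PC discussed or received since contact 1, goes after the second PALCARE so that it does not prime the answers. Use it for description only, since a no-change subgroup of 20 patients would be too small for a useful coefficient.

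The cost is more than rewording. Each interview takes place two weeks later, respondents have completed the items once more before probing (so some first-encounter comprehension problems may be missed), and some interviews will be lost to dropout in a population with advanced cancer.

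If that cost is judged too high for the content-validity work, keep the present order, still correct Aim 3, and report the coefficient as stability across the cognitive interview, not as test-retest reliability. That costs wording only, but leaves test-retest reliability to the later studies.
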